### **12.3 Amendments**

Amendments are changes made to the research after a favourable opinion by the accredited METC has been given. All amendments will be notified to the METC that gave a favourable opinion.

### **12.4 Annual progress report**

The sponsor/investigator will submit a summary of the progress of the trial to the accredited METC once a year. Information will be provided on the date of inclusion of the first subject, numbers of subjects included and numbers of subjects that have completed the trial, serious adverse events/ serious adverse reactions, other problems, and amendments.

### **12.5 Temporary halt and (prematurely) end of study report**

The investigator/sponsor will notify the accredited METC of the end of the study within a period of 8 weeks. The end of the study is defined as the last patient's last visit.

The sponsor will notify the METC immediately of a temporary halt of the study, including the reason of such an action.

In case the study is ended prematurely, the sponsor will notify the accredited METC within 15 days, including the reasons for the premature termination.

Within one year after the end of the study, the investigator/sponsor will submit a final study report with the results of the study, including any publications/abstracts of the study, to the accredited METC.

### **12.6 Public disclosure and publication policy**

Data collected in this trial will be disclosed to the public through peer-reviewed publications and presentations.

### 13. STRUCTURED RISK ANALYSIS

#### 13.1 Potential issues of concern

Not applicable.

a. Level of knowledge about mechanism of action

b. Previous exposure of human beings with the test product(s) and/or products with a similar biological mechanism

c. Can the primary or secondary mechanism be induced in animals and/or in *ex-vivo* human cell material?

d. Selectivity of the mechanism to target tissue in animals and/or human beings

e. Analysis of potential effect

f. Pharmacokinetic considerations

g. Study population

h. Interaction with other products

i. Predictability of effect

j. Can effects be managed?

#### 13.2 Synthesis

The risks that may occur during this trial are risks that are associated with CIC, the aim of this trial is to assess if these risks occur more often when a catheter is reused. Patients will be well trained in the cleaning method, to keep this risk as low as possible. Patients will be informed when to consult a physician. Most patients will have a lot of experience because they are performing CIC for a long period of time already. Patients who are starting CIC will have a learning time of two weeks before they are included in the trial and randomized, so good practice is assured.

If the cleaning method is not accurately performed after extra schooling and there is a high change of infections, patients will be withdrawn from the trial.

# STATISTICAL ANALYSIS PLAN for COMPaRE-trial

---

## ABBREVIATIONS

|        |                                                                           |
|--------|---------------------------------------------------------------------------|
| AE     | Adverse Event                                                             |
| BMI    | Body Mass Index                                                           |
| CE     | Conformité Européenne                                                     |
| CEA    | Cost Effectiveness Analysis                                               |
| CI     | Confidence Interval                                                       |
| CI(S)C | Clean Intermittent (Self) Catheterization                                 |
| COPD   | Chronic Obstructive Pulmonary Disease                                     |
| DM2    | Diabetes Mellitus type 2                                                  |
| EAU    | European Association of Urology                                           |
| FAS    | Full Analysis Set                                                         |
| ITT    | Intention to treat                                                        |
| KC     | Clinical Consult                                                          |
| MAR    | Missing at Random                                                         |
| NA     | Not applicable                                                            |
| NHG    | Nederlandse Huisartsen Gemeenschap (Dutch general practitioner community) |
| NLUTD  | Neurogenic Lower Urinary Tract Dysfunction                                |
| PP     | Per Protocol                                                              |
| PROM   | Patient Reported Outcome Measure                                          |
| QALY   | Quality Adjusted Life Years                                               |
| QoL    | Quality of Life                                                           |
| SAE    | Serious Adverse Event                                                     |
| SD     | Standard Deviation                                                        |
| SOC    | System Organ Class                                                        |
| sUTI   | systemic Urinary Tract Infection                                          |

## STATISTICAL ANALYSIS PLAN for COMPaRE-trial

---

|     |                         |
|-----|-------------------------|
| TC  | Telephone Consult       |
| UTI | Urinary Tract Infection |
| VAS | Visual Analog Scale     |

# STATISTICAL ANALYSIS PLAN for COMPaRE-trial

---

## 2 Introduction

### 2.1 Background and Rationale

Urinary retention affects millions of people worldwide and clean intermittent self-catheterization (CISC) is the preferred treatment. In many high-income countries, single-use plastic catheters is the standard for CISC, with the average individual patient using four catheters daily resulting in approximately 1,825 catheters per year. In the U.S. alone, this generates around 206 million liters of waste annually - equivalent to more than 80 Olympic-size swimming pools. With growing concerns about environmental sustainability and rising healthcare costs, reusable catheters have emerged as a potential alternative. However, the safety and efficacy of reusable catheters, particularly regarding urinary tract infections (UTIs), remain uncertain due to limited quality and conflicting evidence.

This document outlines the planned data summaries and statistical analyses to be performed for the COMPaRE trial: A multicenter, prospective, randomized, non-inferiority study designed to evaluate whether reusable catheters are as safe as single-use catheters for intermittent catheterization in patients with urinary retention. The information presented here is intended to supplement the study protocol, which contains details regarding the objectives and design of the study.

### 2.2 Intervention(s)

#### 2.2.1 Brief description of the study intervention(s)

Patients in the intervention arm will receive instructions and start using the Cliny catheter (males and females) or the PureCath catheter (only females). These reusable catheters can be introduced without lubricant because of a high-quality smooth surface and will be stored in a holder containing a diluted 2% sodium hypochlorite solution, which will be renewed every 24 hours. The 2% sodium hypochlorite solution is diluted with cold tap water (1:80). In this trial, Milton fluid (a product of Procter and Gamble) is used to clean and store the catheter. To reduce the risk of damage from the cleaning solution, the catheter is rinsed with cold tap water before and after each use. Every reusable catheter will be used for 2 weeks. The reusable catheters are Conformité Européenne (CE)-marked which indicates that the manufacturer confirms the product's compliance with European Union legislation for medical devices (Regulation 2017/745). The manufacturer of the reusable catheter (Create Medic) tested the compatibility of cleaning solution with the reusable catheters and recommended the use of 0.6% dilution of 2% sodium hypochlorite w/w solution as cleaning method.

#### 2.2.2 Control settings (if applicable)

Patients allocated to the control arm will remain using their own single-use catheters, the choice of the single-use catheter will be determined by the preference of the patient.

### 2.3 Trial Objectives

#### 2.3.1 Primary Objective

To determine whether reusable catheters are as safe as single-use catheters, measured by UTI/month. The safety analysis, including the (S)AE's will also be presented with the primary results.

#### 2.3.2 Secondary Objectives

# STATISTICAL ANALYSIS PLAN for COMPaRE-trial

Our secondary objectives are to investigate the efficiency and costs-effectiveness of the reusable catheter and to explore patient opinions on the reusable catheter. The table below provides an overview of all objectives and outcome measures.

| Objectives                                                                                                                        | Primary outcome | Secondary outcome                                                                                                                                                                                                                                                          | Measured by                                                                                                                                                                                                                  |
|-----------------------------------------------------------------------------------------------------------------------------------|-----------------|----------------------------------------------------------------------------------------------------------------------------------------------------------------------------------------------------------------------------------------------------------------------------|------------------------------------------------------------------------------------------------------------------------------------------------------------------------------------------------------------------------------|
| Safety
To determine whether reusable catheters are at least not less safe as single use catheters                       | No of sUTIs     | 
 
▶ Hospitalisation due to a sUTI
 
▶ Bacteraemic UTI
 
▶ Urethral damage leading to clinical significant strictures
 
▶ Kidney/bladder stone formation
 
▶ Episodes of macroscopic haematuria
 
 | 
 
▶ sUTI (see definition)
 
▶ sUTI +hospitalisation records
 
▶ sUTI +positive blood culture
 
▶ Anamnestic
 
▶ Anamnestic
 
▶ Anamnestic
 
 |
| Efficiency
To investigate whether reusable catheters are not less efficient as single use catheters                     | X               | 
 
▶ Patient satisfaction
 
▶ Quality of life
 
                                                                                                                                                                        | 
 
▶ PROMs: ISCQ, InCaSaQ, PGI-I
 
▶ PROM: EQ-5D-5L
 
                                                                                                                    |
| Costs-effectiveness
To investigate whether reusable catheters are costs-effective in comparison to single use catheters | X               | 
 
▶ Quality-adjusted-life-years and incremental costs-effectiveness ratios
 
                                                                                                                                                 | 
 
▶ Hospital records
 
▶ PROMs: iMCQ, iPCQ, EQ-5D-5L
 
                                                                                                                  |
| Patient opinions
To explore patients opinions on healthcare costs and environmental burden in the context of CISC       | X               | 
 
▶ Patient opinion
 
                                                                                                                                                                                                        | 
 
▶ Two statement questions answered by a Likert-scale from 1 to 5 (fully agree – fully disagree)
 
                                                                            |

CISC, clean intermittent urinary self-catheterisation; EQ-5D-5L, Euroqol 5 Dimensional 5 Level; iMCQ, iMTA Medical Consumption Questionnaire; InCaSaQ, Intermittent Catheterisation Satisfaction Questionnaire; iPCQ, iMTA Productivity Costs Questionnaire; ISCQ, Intermittent Self-Catheterisation Questionnaire; PGI-I, Patient Global Impression of Improvement; PROMs, patient-reported outcome measurements; sUTI, symptomatic urinary tract infection.

## 3 Trial Methods

### 3.1 Trial Design

The COMPaRE trial is a multicentre randomised non-inferiority trial, conducted at the urological department of the Erasmus Medical Center (Erasmus MC). Patients are randomly assigned according to the minimization method to either single-use catheters (control arm) or reusable catheters (intervention arm).

### 3.2 Randomisation

Randomisation is done by the tool ALEA (meaning ‘dice’ in Latin), according to the regulations of the Erasmus MC. ALEA is developed for randomisation and guarantees concealed allocation. The intervention and control group will be stratified for the participating centres, neurogenic and non-neurogenic causes for catheterisation, age (16–17 years vs  $\geq 18$  years and  $< 50$  years vs.  $\geq 50$  years old), gender, and the female patient group will be balanced for premenopausal and postmenopausal status. On randomisation, patients will be allocated a unique study subject number in chronologically ascending order for every study site, starting with 1 (e.g., Erasmus MC: EMC001). They will be randomized to the intervention arm (reusable catheter) or control arm (single use catheter). There is no prespecified list on randomisation, but each combination of stratification factors will form a combination. Within each combination, ALEA will randomly assign a study arm. The rationale for this approach is that it will maximise the probability of assigning a new participant in

# STATISTICAL ANALYSIS PLAN for COMPaRE-trial

---

the study arm with the lowest number of patients. The company for the randomisation procedure is the Clinical Trial Centre (CTC) of the Erasmus MC.

## 3.3 Statistical Framework

### 3.3.1 Hypothesis Test

This trial is designed to demonstrate the non-inferiority of reusable catheters compared to single-use catheters with regard to the monthly incidence of UTIs over a one-year study period, in patients who perform intermittent self-catheterization due to urinary retention.

- The primary null hypothesis is that reusable catheters are inferior to a single-use catheters with regard to the monthly incidence of UTIs over the study period, with a 7% inferiority margin.
- The alternative null hypothesis is that reusable catheters are non-inferior to a single-use catheters with regard to the monthly incidence of UTIs over the study period, with a 7% inferiority margin.

### 3.3.2 Confidence Intervals and p-values

All calculated p-values will be two-sided and compared to a 5% significance level. If a p-value is less than 0.05, the corresponding treatment group difference will be denoted as statistically significant. All efficacy estimates will be presented with two-sided 95% confidence intervals. As there is only one primary null hypothesis to be tested in this trial, there will be no adjustments for multiplicity.

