### 3.3.3 Decision Rule

This trial is designed to address a single primary outcome. Non-inferiority is claimed if the primary null hypothesis is rejected on the significance level (alpha) of 0.025 (one-sided). That is, if the upper-limit of the two-sided 95% confidence interval for the treatment difference is less than 7%.

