### Overview of Outcomes

| Level     | Outcome                        | Timeframe    | Type        |
|-----------|--------------------------------|--------------|-------------|
| Primary   | UTIs per month                 | During trial | Continuous  |
| Secondary | UTI during follow-up           | During trial | Dichotomous |
|           | Hospitalisation due to UTI     | During trial | Dichotomous |
|           | Bacteraemic UTI/ urosepsis     | During trial | Dichotomous |
|           | Urethral stricture             | During trial | Dichotomous |
|           | Bladder/kidney stone formation | During trial | Dichotomous |
|           | Epididymo-orchitis             | During trial | Dichotomous |
|           | Prostatitis                    | During trial | Dichotomous |

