## 6.2 Methods for secondary outcomes

### 6.2.1 Methods for outcomes of questionnaires (ISCQ, InCaSaQ, EQ-5D-5L, SF-Qualiveen, PGI-I).

#### 6.2.1.1 Descriptive Statistics

Continuous variables will be described using means and standard deviations. Categorical variables will be described using frequency (n) and percentages (%).

Linear mixed models (LMMs) will be used to assess longitudinal trajectories of the PROs between the two treatment arms. The models will include fixed effects for treatment group, time, and the interaction between time and treatment group. Since all questionnaires are collected at the same follow-up scheme, time will be used as a categorical variable (9). To account for within-subject correlation, a random intercept will be included for each patient. Adjustment for confounders is deemed unnecessary, as stratified randomization is applied. Baseline, as well as the scores at 6 weeks, 26 weeks and 52 weeks are included in the model. Longitudinal linear mixed model analyses correct for missing responses at random (9). The interaction between “time x treatment arm” is included in the model as interaction to assess whether the treatment arm had different effects on the outcomes of the questionnaires at different points in time (9).

A post hoc subgroup analysis is conducted to examine outcomes by gender (male vs. female), age

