# STATISTICAL ANALYSIS PLAN for COMPaRE-trial

---

(<65 vs. ≥65 years), and the ethology of lower urinary tract symptoms (LUTS) (neurogenic vs. non-neurogenic origin), using linear mixed-effects models. The model will include fixed effects for treatment arm, gender, age group, and LUTS ethology, as well as interaction terms between the treatment arm and each subgroup variable. Holm's method for multiple comparisons correction will be applied to adjust p-values. The age cut-off is determined based on the median age of the study population.

To facilitate interpretation of changes in the questionnaire scores, effect sizes will be calculated with the use of Cohen's D test. An effect size of 0.3 or less is considered small, more than 0.3 to 0.8 moderate, and more than 0.8 large (10).

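### SAP 3.3.2 labels every p below 0.05 statistically significant and waives multiplicity adjustment, which leaves the questionnaire comparisons unprotected and contradicts the Holm step in SAP 6.2.1.1

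*Combined protocol and SAP*

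**What the plan says.** SAP 3.3.2 sets one rule for every p-value: "All calculated p-values will be two-sided and compared to a 5% significance level". It then fixes the wording of the report: "If a p-value is less than 0.05, the corresponding treatment group difference will be denoted as statistically significant". Its reason for not adjusting is: "As there is only one primary null hypothesis to be tested in this trial, there will be no adjustments for multiplicity".

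The primary outcome has its own rule in SAP 3.3.3. Non-inferiority is claimed "if the upper-limit of the two-sided 95% confidence interval for the treatment difference is less than 7"%, which is a one-sided test at 0.025.

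The SAP's Overview of Outcomes lists the secondary outcomes, from "UTI during follow-up" onward, without ranking them or naming a key secondary. SAP 6.2.1.1 gives the questionnaires a linear mixed model with treatment, categorical time and their interaction, using baseline and weeks 6, 26 and 52. The interaction is there "to assess whether the treatment arm had different effects on the outcomes of the questionnaires at different points in time". Further on in the same section, in the paragraph on a post hoc subgroup analysis, Holm's "method for multiple comparisons correction will be applied to adjust p-values".

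Protocol 10.1 names Chi-square, t and Mann-Whitney tests by type of outcome, with two-sided p-values, and does not mention multiplicity.

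**The concern.** A single primary hypothesis controls the error of the primary claim and nothing else. The primary is judged by a confidence limit against a margin, so in practice the labelling sentence in 3.3.2 governs secondary results. Leaving secondary outcomes unadjusted is acceptable when they are declared exploratory. This SAP instead prescribes the word significant for each nominal p<0.05.

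The two parts of the SAP also disagree: 3.3.2 says there is no adjustment, and 6.2.1.1 makes one. Read together, they protect post hoc subgroup tests and leave the main questionnaire comparisons unprotected.

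In the SAP's table of objectives, satisfaction and quality of life are the only outcomes under the efficiency objective. Protocol section 2 also lists practice recommendations as an objective. A chance difference on one score, in either direction, could be reported as an established finding.

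**Working it through.** **Stated level.** The two-sided 5% critical value and the one-sided 2.5% critical value are both z = 1.960, so 3.3.2 and 3.3.3 agree on the primary. The documents state no family-wise error rate for the secondary outcomes.

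**Which outcomes the SAP compares between arms**

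| Outcome group | Method | Place |
|---|---|---|
| Questionnaire scores | Mixed model with treatment and treatment-by-time terms | SAP 6.2.1.1 |
| (S)AEs | Counts and percentages | SAP 6.1.4.1, 7.1 |
| Patient opinion | Table of responses | SAP 6.2.2.1 |
| Urine cultures | Table of common bacteria | SAP 6.2.3.1 |
| Costs and QALYs | Bootstrap, acceptability curve | SAP 5.3.7 |
| Yes/no clinical outcomes | No test named in the SAP | Overview of Outcomes |

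**Number of tests.** The scores are ISCQ, InCaSaQ, SF-Qualiveen and EQ-5D-5L: four, or five if the EQ-5D index and the EQ VAS are separate. PGI-I is not counted, because protocol 8.1.2 describes it for the intervention group. One test per score gives 4 or 5 tests. One arm contrast at each of weeks 6, 26 and 52 gives 4 × 3 = 12 or 5 × 3 = 15.

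**Chance of at least one false p<0.05 when the arms do not differ.** For k independent tests it is 1 − 0.95^k:
- k = 4: 1 − 0.95⁴ = 0.185
- k = 5: 1 − 0.95⁵ = 0.226
- k = 12: 1 − 0.95¹² = 0.460
- k = 15: 1 − 0.95¹⁵ = 0.537

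Scores from the same patients are correlated. The documents give no correlation, so I simulated equally correlated normal test statistics and counted draws with any |Z| > 1.96:

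| Tests | Correlation 0 | 0.5 | 0.8 |
|---|---|---|---|
| 4 | 0.19 | 0.16 | 0.11 |
| 5 | 0.23 | 0.18 | 0.13 |
| 12 | 0.46 | 0.32 | 0.19 |
| 15 | 0.54 | 0.36 | 0.20 |

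With 15 contrasts and a block structure (0.6 between visits of the same score, 0.3 between scores) the result is 0.42.

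**Against 5%.** One test per score: 0.11/0.05 to 0.23/0.05, about 2 to 5 times. Every visit tested: 0.19/0.05 to 0.54/0.05, about 4 to 11 times.

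**Protocol 10.1.** If its generic tests are also run on the yes/no outcomes, they add to these figures, but rare events add little. With 154 per arm, the Chi-square type I error is 0.7% at an assumed event rate of 0.5% and 3.0% at a rate of 1%.

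**The case against.** The strongest case for the SAP is that it openly states it does not adjust, calls these outcomes secondary, and ties its only claim rule to the primary outcome. It asks for 95% confidence intervals for efficacy estimates and adds effect sizes for the questionnaires. Protocol objective 5 speaks of exploring the patients' perspective. Unadjusted secondary p-values beside a single primary are common, and requiring Holm across them is a matter of judgement. The interaction can also be read as one joint test per score, so 15 separate visit contrasts are possible but are not named.

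Much of this stands. It is why the one-test-per-score range comes first and why mandatory adjustment is not requested. It does not rescue the labelling sentence, which asks for more than exploratory reporting, or the contradiction between 3.3.2 and 6.2.1.1.

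A reader might draw three stronger conclusions, which the documents do not support:
- **That 16 or more secondary outcomes are compared.** The overview table has 18 or 19 secondary rows, depending on how one fused row is read, but it lists outcomes and variable types, not tests. The SAP names a between-arm model only for the questionnaires.
- **That a false significant questionnaire result is likely.** The chance passes one half only with about 15 nearly independent contrasts, which is implausible for repeated scores on the same patients.
- **That the non-inferiority conclusion is at risk.** It rests on the confidence limit in 3.3.3 alone.

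**Conclusion.** The point holds for the questionnaires. Under the rule as written, a trial with no true difference has about an 11 to 23% chance of at least one falsely significant questionnaire result with one test per score, and about 19 to 54% if each post-baseline visit is tested. Both ranges rest on four or five scores and on assumed correlations of 0 to 0.8; the second also assumes visit-by-visit testing, which the SAP leaves open. Even the most favourable case is more than twice the nominal 5%.

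The conflict between 3.3.2 and 6.2.1.1 needs no assumption and has to be reconciled in any event. The primary error rate is unchanged, so this should be corrected but does not undermine the trial's main conclusion.

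**What to change.** Replace both the labelling sentence and the sentence waiving adjustment in SAP 3.3.2. Changing only the first would leave the contradiction in place. Suggested text:

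> The confirmatory claim is limited to the primary outcome under 3.3.3. All secondary comparisons are exploratory, reported as estimates with 95% CIs without multiplicity adjustment, and are not denoted statistically significant. The Holm correction in 6.2.1.1 applies only to the questionnaire subgroup interaction tests.

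State that this also covers any test run under protocol 10.1.

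Optionally, if the sponsor wants a formal questionnaire claim, prespecify one contrast per score and apply Holm across the scores. The first-step threshold is 0.05/4 = 0.0125 for four scores or 0.05/5 = 0.010 for five, and the family-wise error is then at most 5%.

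The cost is SAP wording. Data, visits and sample size do not change. The downside is that some nominal p<0.05 secondary results can no longer be called significant.
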